#### Discontinuing or modifying allocated interventions

Participants may withdraw from the study at any point. Investigators can withdraw participants if it is deemed in their best interest, they engage in protocol deviations placing them at risk, exclusion criteria develop, or an AE occurs that affects their safety.

The Principal Investigator has the right to terminate the study at any time and will make the final decision to terminate the study upon completion. If terminated prematurely, investigators will inform participants promptly, and all requirements regarding the storage and secure destruction of study documents and investigational products will be observed.

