##### Concomitant care

Medications will be reviewed at screening and before the dosing session. If a contraindicated medication is identified at the screening visit, a discussion between the investigators, participant, and their treating practitioner will take place to determine if it is appropriate to cease the medication before the dosing session. This will include a plan for reviewing and, if required, restarting the medication post-psilocybin dosing.

For contraindicated antidepressant medications, the recommendation will be to wean gradually to mitigate discontinuation effects, cease at least five half-lives before the scheduled dosing session to avoid interactions, and restart (if required) after completing the physiotherapy treatment to avoid initial medication titration adverse effects during the treatment course.

Participants will be required to suspend external physiotherapy for their motor FND throughout study enrolment until their study exit.

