**Figure 2. f2:**
[figure not shown]
Study schedule.

**Table 1. tbl1:** Eligibility Criteria

Inclusion criteria	Exclusion criteria
Adults aged 18 to 65 years. A diagnosis of refractory motor FND, supported by relevant neurological investigations and independent assessment by a psychiatrist and neurologist. Motor FND is defined as upper or lower limb motor weakness, gait disorder, or movement disorder (e.g., tremor or dystonia) of at least six months duration. Symptoms are deemed refractory if these are of at least six months duration, persist following physiotherapy and psychiatry management, and are considered by the participant to be impacting their functioning or quality of life. Understanding of their diagnosis of FND. Capacity to provide informed consent for the study.	Medical Exclusion Criteria Cardiovascular conditions: poorly-controlled hypertension, angina, ischaemic heart disease, a clinically significant ECG abnormality, transient ischaemic attack, stroke, or peripheral or pulmonary vascular disease. A diagnosis of epilepsy or previous epileptic seizures. A diagnosis of dementia. Chronic kidney or liver disease. Known conditions putting the participant at risk for hypercalcaemia, Cushing’s syndrome, hypoglycaemia, syndrome of inappropriate antidiuretic hormone secretion, or carcinoid syndrome. Insulin-dependent diabetes; if taking oral hypoglycaemic agents, the participant is only excluded if they also have a history of hypoglycaemia. Females who are pregnant, nursing, or trying to conceive. Use of medications contraindicated with psilocybin, that are inappropriate to cease for the necessary period surrounding the dosing sessions. See section ‘Contraindicated Medications’ for details. Enrolled in another clinical trial involving an investigational product. Psychological Exclusion Criteria Current or previous psychotic disorder, including schizophrenia, schizoaffective disorder, schizophreniform disorder, brief psychotic disorder, delusional disorder, schizotypal personality disorder, substance/medication-induced psychotic disorder, or psychotic disorder due to another medical condition. Current or previous bipolar I or II disorder. First-degree relative with a psychotic or bipolar disorder. A history of attempted suicide or mania. Current or previous substance use disorder (excluding caffeine and nicotine). Previous regular use, or current use, of psychedelic agents. Other psychiatric conditions deemed by research staff to be incompatible with safe exposure to psilocybin.

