### Adherence and retention

Before their study treatment, participants will receive a detailed appointment handout, which also reiterates pre- and post-dosing requirements and recommendations. Travel costs incurred for attending each study visit will be reimbursed, up to $50 per visit, and food and drink will be provided at the dosing session. No additional financial inducements will be provided. The psychiatry follow-up visits and qualitative interview will be offered either in person or via video call, as per participant preference, to promote retention by reducing the required number of in-person visits. The study team will monitor data in real time to ensure completeness and will document attempts to obtain follow-up data and any protocol deviations.

To assess the fidelity of the physiotherapy treatment (the extent to which the treatment followed the intervention protocol):The study physiotherapist will complete a checklist for each participant, based on the template for intervention description and replication (TIDieR) checklist description (Hoffmann *et al*., 2014).The content, length, and number of physiotherapy sessions by participant report will be monitored with a structured telephone survey following completion of the physiotherapy treatment.A random sample of completed physiotherapy workbooks will be assessed by an independent physiotherapist against predetermined criteria.

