### Statistical methods

Prior to the study database being locked, a comprehensive statistical analysis plan will be finalised. The analysis will encompass all participants who were randomised, regardless of whether they completed their full study enrolment. All available data from these participants will be included. The reasons for any participant’s early withdrawal from the study will be documented.

An interim analysis using unblinded data will be performed after 50% (*n* = 12) of the target sample size has completed their study enrolment. This analysis will consist of summary statistics of tolerability and efficacy outcomes by treatment groups. These interim results will support planning for a follow-up RCT in motor FND participants. As such, the goal of the interim analysis is not related to this pilot study, and no sample size adjustment will be made as a result. Blinding will be maintained as described earlier.

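### Withdrawal is the only stated action for an individual after the single dose, so later symptom and new adverse-event data could be lost selectively in those who tolerate treatment poorly

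*Protocol article*

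**What the plan says.** All references are to the protocol article.

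- **Discontinuing or modifying allocated interventions.** The section opens with "Participants may withdraw from the study at any point". Investigators may then withdraw someone in their best interest, or if "they engage in protocol deviations placing them at risk, exclusion criteria develop, or an AE occurs that affects their safety". No time limit is given. Despite the heading, no lesser action for an individual appears in this section.
- **Statistical methods.** All randomised participants are analysed with whatever data are available. The reasons for any participant's "early withdrawal from the study will be documented".
- **Adherence and retention.** The team "will document attempts to obtain follow-up data and any protocol deviations". The section does not say whether this covers withdrawn participants.
- **Treatment** and **Primary outcomes.** There is one dosing session, followed by six physiotherapy sessions within three weeks. The S-FMDRS is due at baseline, at the end of physiotherapy, and one and four weeks later. The 15 mg arm also has it at 1.5 and 4.5 hours after dosing. The PGI scales are due on treatment mornings and at the same three later visits. New adverse events are recorded while the study lasts.
- **Adverse event reporting and harms.** Events that have occurred are followed to resolution, or further follow-up is arranged.
- **Sample size.** Replacement is provided only for those who withdraw before dosing.

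**The concern.** Before dosing, withdrawing someone who develops an exclusion criterion protects them, and eligibility is rechecked on the dosing day. After the single dose there is no further drug exposure to prevent, and the trigger can select on harm. The exclusion list in Table 1 includes "substance/medication-induced psychotic disorder, or psychotic disorder due to another medical condition", as well as "A history of attempted suicide or mania" and stroke. If one of these arose after dosing, it would be both a possible harm of treatment and a ground for removing the participant.

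Tolerability, S-FMDRS change and PGI change, within and between arms, are all primary aims. If removal follows poor tolerability, the observed symptom change describes those who stayed, and new adverse events in those removed may go unrecorded. The article itself notes concern about incomplete adverse-event reporting in this field, and the results are meant to inform a powered trial.

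**Working it through.** The plan gives no figure on this point. Its one stated probability, over 90% for at least one non-completer among 12, answers another question. It reproduces (1 − 0.8^12 = 93.1%) and is not affected. The check here is a reading of the text, followed by arithmetic on the schedule.

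**Which reading?** The sentence on investigators does not repeat the words about leaving the study. The sentence before it does, and *Statistical methods* uses the same notion for early withdrawal. Study withdrawal is therefore the natural reading, though not the only possible one.

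**What survives such a withdrawal?** The triggering event, followed to resolution; dosing-day vital signs and, in the 15 mg arm, task completion; PGI ratings up to that day; the reason; and a place in the analysis. No section provides for later S-FMDRS, PGI or new adverse-event assessment, and *Follow-up* returns participants to usual care at study exit.

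**S-FMDRS.** Scheduled post-dose assessments are 3 in the 25 mg arm, and 2 + 3 = 5 in the 15 mg arm.

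| Withdrawn | Shared visits lost | Left, 25 mg | Left, 15 mg |
|---|---|---|---|
| Before end-of-treatment visit | 3 of 3 | 0 of 3 | 2 of 5, both during acute drug effects |
| After it, before one week | 2 of 3 | 1 of 3 | 3 of 5 |
| After one week, before four weeks | 1 of 3 | 2 of 3 | 4 of 5 |

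Each participant in the first row removes 1/12 = 8.3% of that arm's S-FMDRS data from the end of treatment onward.

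**PGI.** Assuming six sessions on six separate days, there are 6 + 3 = 9 post-dose assessments. Someone withdrawn after two sessions keeps 2 of 9.

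**Adverse-event observation.** Let the physiotherapy course end on day L after dosing, with L at most 21. Scheduled observation lasts L + 28 days. Withdrawal on day d ≤ L loses (L + 28 − d)/(L + 28), which is at least 28/(L + 28):

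- L = 7: 28/35 = 80%
- L = 14: 28/42 = 67%
- L = 21: 28/49 = 57%

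The bound falls as L grows, so the loss is at least 57% for any permitted course length.

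**Illustration only.** The document gives no withdrawal rate and no outcome SD. Assume that 1 to 3 of 12 in an arm are withdrawn after dosing and that their mean change is 0.5 to 1.0 SD worse than in those retained. The observed-case arm mean is then too favourable by (k/12) × difference: from 1/12 × 0.5 = 0.04 SD to 3/12 × 1.0 = 0.25 SD. The standard error of an arm mean is 1/√12 = 0.29 SD, so even the upper end is smaller than sampling error. This is not an estimate for this trial.

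**The case against.** The strongest reply is that this is a condensed article. It never says that assessment stops at withdrawal, and the full protocol may provide for continued follow-up. Withdrawal is also discretionary and led by the participant's best interest. A reader might infer that the plan ends data collection in withdrawn participants, or drops them from the analysis. The document does not support the first and contradicts the second. A reader might also infer that the results will look too favourable. That is unsupported, because neither the number of withdrawals nor the difference in outcome is known. What remains is that the article states a rule here and is not merely silent, and the rule as worded permits the loss.

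Second, tolerability is partly protected. There is a safety call the day after dosing, the triggering event is followed, and the reason is recorded. Common acute events are described as mostly transient, so a share of observation days overstates the share of information lost. This stands, and it limits the adverse-event part to new, later events.

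Third, in the gravest cases investigators need freedom to act, and an S-FMDRS score after a stroke would not cleanly measure FND change. This also stands. Any amendment must keep that discretion.

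Fourth, one might infer that early stoppers would be barred from restarting antidepressants, because *Concomitant care* advises to "restart (if required) after completing the physiotherapy treatment". That goes too far: the timing is a recommendation, and a plan for review and restart is already required.

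**Conclusion.** The point holds as a cheap improvement and is not a fatal flaw. After the single dose, the stated rule allows withdrawal for an adverse event or a developed exclusion criterion, and the article offers no route to stop treatment and remain in follow-up. On the natural reading this permits selective loss of later primary-outcome data. Its size is known only per withdrawn participant: up to three of three shared S-FMDRS visits, and at least 57% of scheduled adverse-event observation if withdrawal comes by the end of the course. The frequency and any bias are unknown. The conclusion rests on reading withdrawal as leaving the study and on no contrary rule in the full protocol. If that document already continues follow-up, one clarifying sentence is enough. The trial is an open-label pilot that already limits its therapeutic conclusions, which keeps the weight low.

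**What to change.** 1. Amend *Discontinuing or modifying allocated interventions*. After dosing, an adverse event affecting safety, a developed exclusion criterion or a risky protocol deviation stops the remaining physiotherapy or movement tasks. Adverse-event, PGI and S-FMDRS assessments continue at the planned end-of-treatment, one-week and four-week visits (at latest about days 21, 28 and 49 after dosing), unless the participant withdraws consent or an assessment is clinically unsafe.
2. Keep best-interest withdrawal from the study as an exception, with the reason recorded.
3. Amend *Concomitant care*, which now says "Participants will be required to suspend external physiotherapy for their motor FND throughout study enrolment until their study exit". Let that ban end when study physiotherapy stops. This is needed only because of change 1: someone who stops on day 7 of a 21-day course and is followed to day 49 could otherwise go up to 49 − 7 = 42 days without FND physiotherapy. Record any outside physiotherapy or restarted medication. The antidepressant advice needs no rewording.

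**Cost.** Wording changes in two sections and no new visit types. Each early stopper adds up to three in-person assessments, because the study physiotherapist rates the primary S-FMDRS; psychiatry visits may be by video. Later scores in early stoppers may reflect outside care and should be reported as such. No sample-size figure changes.

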#### Concomitant care

##### Contraindicated medications

To be enrolled in the study, participants must not be taking:Opioids within 12 hours of psilocybin dosing.Antidepressants within five half-lives of their cessation before psilocybin dosing.Potent enzyme inducers or inhibitors.Drugs with a narrow therapeutic index within 12 hours of psilocybin dosing.Nicotine and caffeine within 2 hours before and 6 hours following psilocybin dosing.

##### Concomitant care

Medications will be reviewed at screening and before the dosing session. If a contraindicated medication is identified at the screening visit, a discussion between the investigators, participant, and their treating practitioner will take place to determine if it is appropriate to cease the medication before the dosing session. This will include a plan for reviewing and, if required, restarting the medication post-psilocybin dosing.

For contraindicated antidepressant medications, the recommendation will be to wean gradually to mitigate discontinuation effects, cease at least five half-lives before the scheduled dosing session to avoid interactions, and restart (if required) after completing the physiotherapy treatment to avoid initial medication titration adverse effects during the treatment course.

Participants will be required to suspend external physiotherapy for their motor FND throughout study enrolment until their study exit.

#### Outcomes

Time points for all outcome measures are outlined in Fig. 2, and their details are provided in Table 2.

**Figure 2. f2:**
[figure not shown]
Study schedule.

**Table 1. tbl1:** Eligibility Criteria

Inclusion criteria	Exclusion criteria
Adults aged 18 to 65 years. A diagnosis of refractory motor FND, supported by relevant neurological investigations and independent assessment by a psychiatrist and neurologist. Motor FND is defined as upper or lower limb motor weakness, gait disorder, or movement disorder (e.g., tremor or dystonia) of at least six months duration. Symptoms are deemed refractory if these are of at least six months duration, persist following physiotherapy and psychiatry management, and are considered by the participant to be impacting their functioning or quality of life. Understanding of their diagnosis of FND. Capacity to provide informed consent for the study.	Medical Exclusion Criteria Cardiovascular conditions: poorly-controlled hypertension, angina, ischaemic heart disease, a clinically significant ECG abnormality, transient ischaemic attack, stroke, or peripheral or pulmonary vascular disease. A diagnosis of epilepsy or previous epileptic seizures. A diagnosis of dementia. Chronic kidney or liver disease. Known conditions putting the participant at risk for hypercalcaemia, Cushing’s syndrome, hypoglycaemia, syndrome of inappropriate antidiuretic hormone secretion, or carcinoid syndrome. Insulin-dependent diabetes; if taking oral hypoglycaemic agents, the participant is only excluded if they also have a history of hypoglycaemia. Females who are pregnant, nursing, or trying to conceive. Use of medications contraindicated with psilocybin, that are inappropriate to cease for the necessary period surrounding the dosing sessions. See section ‘Contraindicated Medications’ for details. Enrolled in another clinical trial involving an investigational product. Psychological Exclusion Criteria Current or previous psychotic disorder, including schizophrenia, schizoaffective disorder, schizophreniform disorder, brief psychotic disorder, delusional disorder, schizotypal personality disorder, substance/medication-induced psychotic disorder, or psychotic disorder due to another medical condition. Current or previous bipolar I or II disorder. First-degree relative with a psychotic or bipolar disorder. A history of attempted suicide or mania. Current or previous substance use disorder (excluding caffeine and nicotine). Previous regular use, or current use, of psychedelic agents. Other psychiatric conditions deemed by research staff to be incompatible with safe exposure to psilocybin.

Abbreviations: ECG, Electrocardiogram; FND, Functional neurological disorder.

**Table 2. tbl2:** Primary, Secondary, and Exploratory Outcomes

	Domain	Measures	Administration	Application and clinical relevance
**Primary Outcomes**	Tolerability	Vital signs	Clinician-administered	Heart rate, blood pressure, and oxygen saturation on room air will be monitored.
		Adverse events form	Clinician-administered	Treatment-emergent adverse events will be recorded in the adverse events form. These will be classified based on the type, number, severity, relatedness to the study drug, and whether the event constitutes a serious adverse event or significant safety issue.
	Feasibility	Completion of movement tasks	Clinician-administered	The S-FMDRS (Nielsen *et al.,* 2017a), DEMMI (de Morton *et al*., 2008), FME, ARAT (Yozbatiran *et al*., 2008), and BBT (Mathiowetz *et al*., 1985) (original and modified versions) measure several domains of motor function to assess the feasibility of competing movement tasks during the acute drug effects.
	Symptom severity	S-FMDRS	Clinician-administered	9-item instrument assessing seven body regions and two functional movements commonly affected in motor FND (Nielsen *et al.,* 2017a). Severity and duration are each rated from 0 to 3 for each of the nine items, with scores summed to provide a total score between 0 to 54 (higher scores indicate greater impairment).
		PGI-S & -I	Self-administered	PGI-S: 1-item instrument, scored from 1 to 4 (higher scores indicate greater severity), assessing disease severity (Food & Drug Administration, 2018). PGI-I: 1-item instrument rated from 1 to 7 (lower scores indicate greater improvement and higher scores indicate worsening) assessing change following an intervention (Mohebbi *et al*., 2018; Remigio-Baker *et al*., 2024).
**Secondary Outcomes**	Symptom severity	S-FMDRS – video assessment	Clinician-administered	Clinician-rated severity of functional motor symptoms, graded through video assessment by a blinded, independent assessor.
		CGI-S & -I	Clinician-administered	CGI-S: 1-item instrument, scored from 1 to 7, assessing disease severity (higher scores indicate greater severity) (Busner & Targum, 2007). CGI-I: 1-item instrument rated from 1 to 7 assessing change following an intervention (lower scores indicate greater improvement and higher scores indicate worsening) (Busner & Targum, 2007).
	Co-occurring symptoms	PHQ-9	Self-administered	9-item scale, scored from 0 to 3, assessing the severity of depressive symptoms over the past two weeks (higher scores indicating greater frequency of symptoms) (Kroenke *et al*., 2001). Items are summed to provide a total score between 0 to 27. An additional 10^th^ item is provided to ascertain the impact on functioning, scored 1 to 4 (higher scores indicating greater impairment).
		GAD-7	Self-administered	7-item scale, scored from 0 to 3, assessing the severity of anxiety symptoms over the past two weeks (higher scores indicating greater frequency of symptoms) (Spitzer *et al*., 2006). Items are summed to provide a total score between 0 to 21. An additional 8^th^ item is provided to ascertain the impact on functioning, scored 1 to 4 (higher scores indicating greater impairment).
		PHQ-15	Self-administered	15-item scale, scored from 0 to 2, assessing the impact of various somatic symptoms over the past week (higher scores indicate greater impact) (Kroenke *et al*., 2002). Items are summed to provide a total score between 0 to 30.
	Quality of life	SF-36	Self-administered	36-item scale, grouped into 8 subscales representing core health-related quality of life dimensions (physical functioning, role limitations due to physical health, pain, general health, emotional wellbeing, social functioning, role limitations due to emotional problems, energy/fatigue, and mental health) (Ware *et al*., 1993). Item responses range from the lowest option at 1 to the highest option from 2 to 6 (depending on the item), with reverse scoring for some items. Each item is then converted to a 0 to 100 range, with higher scores indicating a more favourable health state.
	Treatment expectations	SETS	Self-administered	6-item scale, 3 each for positive and negative expectations, and each item scored on a 7-point Likert scale (lower scores indicate greater disagreement and higher scores indicate greater agreement) (Younger *et al*., 2012).
	Drug intensity	5D-ASC	Self-administered	94-item scale across 11 subscales (de Deus Pontual *et al*., 2023). Responses are rated on a visual analog scale, from ‘No, not more than usually’ to ‘Yes, much more than usually’. Items are summed for each subscale to provide a total score. Higher scores indicate greater alterations in states of consciousness.
		EDI	Self-administered	8-item focused assessment of the experience of ego-dissolution (Nour *et al*., 2016). Each item is rated on a visual analog scale from ‘No, not more than usually’, to ‘Yes, entirely or completely’. Scores are provided for each item and summed to provide a total score. Higher scores indicate greater ego-dissolution.
**Exploratory Outcomes**	Movement tasks	DEMMI	Clinician-administered	15-item unidimensional instrument that assesses mobility from bed-bound to independent mobility, including balance, gait, seating, and strength (de Morton *et al*., 2008). Eleven items are dichotomous (scored 0 or 1), and four items have three response options (scored 0, 1, or 2) based on ability and time to completion (lower scores indicate greater impairment). Raw scores (from 0 to 19) are converted to a total DEMMI score (0 to 100) as defined by the scoring key. Additional comments for duration are provided where relevant.
		FME	Clinician-administered	FND extension module developed by our team, assessing movements incorporated in the physiotherapy intervention used in this study (Nielsen & Holt, 2024), to assess additional movements, including standing up from a chair, weight shifting, and balance. Items are dichotomous (scored 0 or 1) based on ability (lower scores indicate greater impairment). Items are summed to provide a total score between 0 to 4. Additional comments for duration are provided where relevant.
		ARAT	Clinician-administered	19-item instrument assessing upper limb coordination, dexterity, and functioning (lower scores indicate greater impairment) (Yozbatiran *et al*., 2008). Items are scored from 0 to 3 (lower scores indicate greater impairment). Scores are provided for four subscales, defined as grasp (sum of six items, range 0 to 18), grip (sum of four items, range 0 to 12), pinch (sum of six items, range 0 to 18), and gross movement (sum of three items, range 0 to 9). Items are summed to provide a total score from 0 to 57.
		BBT – original and modified	Clinician-administered	Original – movement of blocks from one box to another over 60 s, assessing unilateral gross manual dexterity. It has shown high test–retest validity from normative data in adults without disability (Mathiowetz *et al*., 1985). Modified – as above, but with a shield placed between the participant’s vision and their hands and access to a mirror to view their movements via reflection. This modulates attentional mechanisms of movement – an important feature of motor FND management. Lower scores for each scale are indicative of greater impairment. Lower scores for each scale are indicative of greater impairment.
		Video footage	Clinician-administered	Review of video footage of movement tasks to assess movement quality.
	Sensorimotor function	Force-matching task	Clinician-administered	Force-matching performance and sensory attenuation caused by self-generated movement (Pareés *et al*., 2014).
	Brain activity	Resting-state fMRI	Clinician-administered	Resting-state measures of brain activity (McCulloch *et al*., 2022).
		Task-based fMRI	Clinician-administered	Measures of brain activity during a Bayesian-belief updating task (Sharot *et al*., 2011; Korn *et al*., 2014; Marks & Baines, 2017).
	Personality	BFI-2	Self-administered	60-item scale based on the five-factor model of personality (Soto & John, 2017). Items are scored on a 5-point Likert scale (lower scores indicate greater disagreement and higher scores indicate greater agreement, with reverse option wording across some items). Items are summed for 5 domains and 15 facet subscales.
	Subjective experiences	Perspectives on study treatment	Self-administered	9-item questionnaire including responses on ordinal scales, a visual analog scale, and free-text, exploring perspectives on aspects of the study treatment, including physiotherapy and psilocybin.
		Qualitative interview	Self-administered	Qualitative interview exploring subjective experiences of psilocybin, completing movement tasks during the acute drug effects, and the study treatment.

Abbreviations: 5D-ASC, 5-Dimensional Altered States of Consciousness; ARAT, Action Research Arm Test; BBT, Box and Block Test; BFI-2, Big Five Inventory-2; CGI-I, Clinical Global Impressions of Improvement; CGI-S, Clinical Global Impressions of Severity; DEMMI, De Morton Mobility Index; EDI, Ego-Dissolution Inventory; FME, Functional Movement Exploration; fMRI, Functional magnetic resonance imaging; GAD-7, General Anxiety Disorder-7; PGI-I, Patient’s Global Impressions of Improvement; PGI-S, Patient’s Global Impressions of Severity; PHQ-9, Patient Health Questionnaire-9; PHQ-15, Patient Health Questionnaire-15; S-FMDRS, Simplified Functional Movement Disorder Rating Scale; SETS, Stanford Expectations of Treatments Scale; SF-36, 36-Item Short-Form Health Survey.

